#### Lifestyle Factors, Psychological Status, and Sexual Function

Lifestyle factors, psychological status, and sexual function were evaluated multidimensionally using structured self-administered questionnaires, incorporating validated scales and specific self-developed questions. Where available, validated Japanese versions or established Japanese translations of standard instruments were used. Regarding lifestyle habits, data on smoking habits (Brinkman index; daily number of cigarettes × years) [53], alcohol consumption (Alcohol Use Disorders Identification Test–Consumption [AUDIT-C]) [54], and sauna/bathing habits (self-developed questionnaire) were collected. Nutritional intake was assessed using the Brief-type Self-Administered Diet History Questionnaire (BDHQ) [55]. Sleep quality was evaluated using the Japanese version of the Pittsburgh Sleep Quality Index (PSQI-J) [56], chronotype using the reduced Morningness-Eveningness Questionnaire (rMEQ) [57], and physical activity levels using the International Physical Activity Questionnaire (IPAQ) [58].

Psychological status was assessed using the Perceived Stress Scale (PSS) [59] and the Kessler Psychological Distress Scale (K6) [60]. Sexual function and urological symptoms were comprehensively evaluated using the Sexual Health Inventory for Men (SHIM) [61,62], a modified SHIM replacing “sexual intercourse” with “masturbation” in questions 3-5 [63]; the Erection Hardness Score (EHS) [64,65]; the Male Sexual Health Questionnaire–Ejaculatory Dysfunction–Short Form (MSHQ-EjD-SF) [66,67]; and a modified version of the first question of the MSHQ-EjD-SF, where “sexual intercourse” was replaced with “masturbation” (self-developed modification). The self-estimated intravaginal ejaculation latency time [68] and the self-estimated ejaculation latency time during masturbation (self-developed question) were additionally assessed. The frequencies of sexual intercourse, masturbation, nocturnal erection, and feelings of sexual desire were evaluated using point scales similar to those used in the 2023 National Survey in Japan [69].

Furthermore, the Aging Males’ Symptoms Scale (AMS) score [70-72] was used as an indicator of physical and psychological changes associated with androgen decline. The National Institutes of Health Chronic Prostatitis Symptom Index (NIH-CPSI) [73] was used to evaluate chronic prostatitis symptoms. These measures were included to support exploration of potential infertility risk factors and hypothesis generation.

Published studies support the reliability/validity or relative validity of the BDHQ [55], PSQI-J [56], rMEQ [57], IPAQ [58], AUDIT-C [54], PSS [59], K6 [60], AMS [71], and NIH-CPSI [73] in Japanese populations. A Japanese version of the SHIM [62] and MSHQ-EjD-SF [67] were used. The EHS is a single-item measure, for which internal consistency is not applicable. Modified or self-developed items were treated as exploratory measures.

#### Physical Measurements

For group 2 participants, we conducted detailed physical function evaluations and physical measurements based on standardized procedures. The weight, BMI, body fat percentage, muscle mass, and segmental muscle mass of the limbs and trunk were measured using a multifrequency body composition analyzer (MC-780A, TANITA, Tokyo, Japan). The skeletal muscle mass index [74], fat mass index [75,76], phase angle [77,78], and extracellular water–to–total body water ratio [79] were also measured. These indicators were collected to evaluate the detailed body composition, including regional characteristics and cellular status, in addition to indicators such as BMI and body fat percentage commonly used in previous studies [80,81]. Measurements were performed with participants barefoot and wearing light clothing, with corrections made for the weight of the clothing.

Subsequently, muscle strength was evaluated as a physical indicator of androgen status and whole-body muscle strength. In addition to grip strength [82,83], a widely used representative indicator of whole-body muscle strength and physical function, back muscle strength [84] was also measured for a more comprehensive evaluation of muscle strength status, including that of the trunk. Digital grip strength (TAKEI 5401, SANKA Co, Ltd, Health Equipment Division, Tokyo, Japan) and back muscle strength meters (TAKEI 54021, SANKA Co, Ltd) were used. Grip strength was measured twice for each hand alternately in the standing position, and the maximum value was adopted [85]. Back muscle strength was measured twice, with the upper body inclined forward at 30° and the knees extended (but not locked), and the maximum value was adopted [86].

Anatomical circumferences were measured based on standardized procedures using a nonstretchable measuring tape (SECA 201, Hamburg, Germany). Specifically, the waist circumference was measured at the midpoint between the lower rib margin and the iliac crest [87]. The maximum circumferences of the hip [88], thigh [89], and calf [90] were also measured. These circumferences were collected exploratorily for a simple evaluation of the regional body shape and fat/muscle distribution, which could not be captured using whole-body composition indicators. For quality control, each site was measured twice, and if the difference was ≥1 cm, a third measurement was performed. Sexual function may be associated with complex physical factors, such as systemic metabolic status, muscle mass/strength, fluid distribution, and physical activity. Thus, data on body composition, muscle strength, and morphological indicators were comprehensively collected to evaluate the whole-body physical status multidimensionally.

#### Semen Analysis and Subjective Assessment

Following an ejaculatory abstinence period of 48 to <144 h (verified upon arrival) [91], semen was collected via masturbation in a designated room at the clinical research facility and analyzed in an onsite laboratory. The samples were liquefied in a 37°C incubator or at room temperature, with a maximum liquefaction time of 60 minutes. Incomplete liquefaction was defined as a thread length of ≥2 cm during pipetting, in which case mechanical agitation using an 18-gauge needle was performed. Semen volume was calculated by weighing the collection container, assuming a semen density of 1.0 g/mL.

Semen analysis was performed using an automated semen quality analysis system (LensHooke X3 PRO, Bonraybio, Taichung, Taiwan) [92]. Sperm concentration and total motility were measured in accordance with the 6th Edition of the *World Health Organization (WHO) Manual for Human Semen Analysis* [93,94]. The following specific kinematic parameters were also analyzed: categorization of sperm motility (fast progressively motile, slow progressively motile, nonprogressively motile, and immotile), average path velocity, straight line velocity, curvilinear velocity, amplitude of lateral head displacement, beat cross frequency, linearity, straightness, and wobble [95]. In addition, the percentage of normal morphology, pH, and round cell concentration were measured using an automated image recognition system. To evaluate sperm oxidative stress, the static oxidation-reduction potential was measured using a sperm oxidative stress measurement system (MiOXSYS, Caerus Biotech, Vilnius, Lithuania) [96]. Microscopic videos generated by the system were stored in native output format, and file metadata (eg, frame rate and resolution) were retained for subsequent image-based analyses.

The participants additionally completed a Subjective Assessment at Collection questionnaire immediately after semen collection. The questionnaire recorded the abstinence period, presence of spillage, time taken for collection on the study day, subjective intensity of orgasm on the study day (4-point Likert scale) [97], subjective semen volume compared to usual (modified question 3 of the MSHQ-SF), subjective time taken for collection compared to usual (self-developed question), and stress level during collection (10-point Likert scale, self-developed question). This was intended to aid in assessing the influence of psychological and situational factors on sample quality.

Residual samples after analysis were preserved as smears for Diff-Quik staining. Residual semen for downstream exploratory analyses was aliquoted according to the volume available after onsite testing and stored at −80°C before shipment to collaborating institutions or external laboratories. The smears are being morphologically evaluated based on Kruger’s strict criteria [98]. Depending on residual sample availability, frozen semen aliquots are being used for exploratory analyses of the sperm DFI; high DNA stainability (HDS) using SCSA [99-101]; trace and major elements and chemical speciation elements in semen and seminal plasma; and additional biomarkers, such as inhibin B and insulin-like 3 (INSL3).

#### Blood and Urine Assays

Group 2 participants provided early-morning urine and fasting blood samples. Fasting was defined as no breakfast on the study day, and the participants were instructed to finish dinner by approximately 9:00 P.M. on the day before the visit. Water intake was permitted. To account for diurnal fluctuations in analytes, such as testosterone [102] and zinc [103] levels, blood samples were collected between 8:00 and 11:00 A.M. To avoid potential alterations in parameters such as postejaculation prolactin, blood sampling was performed before semen collection [104]. A portion of the blood was processed into plasma or serum and stored frozen at −80°C; these samples were shipped to collaborating institutions or external laboratories for exploratory analysis.

Urine assays include measurements of exposure to environmental chemicals (phthalate esters, parabens, and pesticides), soy isoflavones, trace and major elements, chemical speciation of elements, creatinine, specific gravity, and urea nitrogen. Blood assays include measurements of serum and plasma gonadotropins and sex steroid profiles (follicle-stimulating hormone, luteinizing hormone, testosterone, free testosterone, dehydroepiandrosterone sulfate, sex hormone–binding globulin, dihydrotestosterone, estradiol, prolactin, anti-Müllerian hormone, inhibin B, and INSL3), metabolic markers (serum albumin, fasting blood glucose, and insulin), and selected exposure substances (per- and polyfluoroalkyl substances, trace and major elements, and chemical speciation of elements) in whole blood, serum, and plasma.

#### Definition of Outcome Measures

The primary outcome measure is the continuous DFI. The DFI refers to the proportion of sperm with fragmented or acid-denaturable DNA. In this study, the DFI is measured using SCSA after acid treatment and acridine orange staining with flow-cytometric analysis [12-14]. The primary analysis will assess whether predefined microscopic sperm image-/video-derived summary variables are associated with a continuous DFI, as a feasibility-oriented proof-of-concept evaluation of whether sperm microscopy data contain information relevant to sperm DNA integrity. Secondary and exploratory outcome measures include a categorical DFI based on literature-informed or study-specific exploratory thresholds, HDS, and general semen analysis parameters. Clinical, environmental, physical, and lifestyle variables will be examined as candidate correlates or confounders in secondary exploratory analyses [105].

### Statistical Analysis

#### Descriptive Statistics and Data Preprocessing

Continuous variables will be summarized as means (SDs) and/or medians (IQRs), depending on the distribution characteristics, and categorical variables will be summarized as frequencies (percentages) [106]. The DFI will be treated as a continuous variable. Categorization using literature-informed thresholds (eg, 15% and 27%) [107-110] will also be used in secondary exploratory analyses. In addition, if data characteristics permit, a study-specific candidate threshold will be explored using receiver operating characteristic (ROC) analysis against a prespecified binary semen quality classification based on the lower fifth percentile values for basic semen parameters described in the 6th Edition of the *WHO Manual for Human Semen Analysis* [94,111,112]. Any such data-driven threshold will be considered hypothesis generating only [113].

No formal between-group inferential comparison between groups 1 and 2 is a primary objective of this study. Any comparison of baseline characteristics between the two groups will therefore be descriptive/exploratory only. If participant overlap between groups is present, co-enrolled individuals will be counted only once in such cross-group summaries or in any pooled participant-level analysis requiring independence. Under the primary handling rule, the group 1 record will be retained and the corresponding group 2 record excluded, because group 1 had stricter eligibility criteria and a quality control purpose. Alternative handling rules, such as retaining the group 2 record or excluding co-enrolled participants entirely, may be examined as sensitivity analyses. This issue does not affect the main group-specific analyses, in which group 1 is used for DFI quality control and group 2 for exploratory association analyses.

All statistical tests will be two-sided and interpreted using a nominal significance level of *P*<.05. However, the secondary analyses are exploratory and involve multiple related comparisons and sensitivity analyses. Thus, emphasis will be placed on effect sizes, 95% CIs, and consistency of direction rather than on statistical significance alone, and no formal multiplicity adjustment is planned. As exposure indices (eg, environmental chemicals) may generally exhibit skewness, transformations (eg, logarithmic transformations) will be considered according to the distribution [114]. For urinary indices, a correction using urinary creatinine or specific gravity will be applied [115,116].

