**Methods:**

This multi-institutional cross-sectional study centralized clinical assessment and specimen collection at a single site in Japan. The prespecified group-specific enrollment targets were 25 for group 1 (a relatively homogeneous low-risk cohort for DFI quality control) and 100 for group 2 (apparently healthy community-based adult volunteers for exploratory association analyses). Microscopic sperm videos, automated semen parameters, and sperm oxidative stress data were obtained at collection. SCSA-based DFI assays are currently being performed sequentially. Group 2 participants additionally provided fasting blood and early-morning urine samples for endocrine, metabolic, environmental chemical, and elemental assays. They also underwent physical measurements and completed structured questionnaires/interviews on lifestyle, nutrition, sleep, psychological status, sexual function, and collection conditions. The primary outcome measure is the continuous DFI assessed with SCSA. Group 1 data will be used to evaluate intraday, interday, and interfacility variability and to fix flow cytometry gating settings. In groups 1 and 2, predefined image-/video-derived summary variables after standardized preprocessing will be analyzed against the continuous DFI using correlation analyses and simple linear regression to assess whether sperm microscopy data contain information relevant to sperm DNA integrity. Exploratory categorical DFI analyses will use simple logistic regression. Secondary exploratory analyses will examine candidate covariates and data completeness, including sensitivity analyses.

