### Study Objectives

This protocol paper describes the initial phase of the Nippon Semen and Environmental Exposure Database (N-SEED) initiative as a multicenter cross-sectional study. N-SEED is designed as a long-term, scalable database infrastructure and is not intended to be completed in a single year. As a preliminary step, the 2026 project prospectively collected biospecimens (urine, blood, and semen) and related data (semen analysis, physical measurements, and questionnaire/interview data) from apparently healthy community-based adult men. These data will be used to statistically evaluate the associations between sperm microscopy image/video data and sperm functional assessment measures, including the DFI. The ultimate long-term goal is to support the development and validation of image-based male fertility assessment technologies. This initial phase focuses on data collection feasibility, measurement quality control, and analytical readiness. Accordingly, this initial phase is not intended to develop or externally validate a clinically deployable AI model. Rather, it is intended to establish standardized acquisition and quality control procedures; estimate the magnitude and variability of image-DFI associations; identify candidate confounders and features; and inform formal sample-size planning, model development, and independent validation strategies for later phases. Specifically, we will conduct a preliminary assessment focusing on three key aspects:

First, we will evaluate interfacility variability and perform intrafacility quality control of the DFI testing method. In group 1, which is designed primarily for quality control of DFI testing, we will assess the reliability of the measurement system.Second, we will prospectively collect standardized microscopic sperm videos and related multimodal data. Initial association analyses between sperm image/video data and the DFI will then be conducted to evaluate feasibility and inform subsequent study design (groups 1 and 2).Finally, we will explore multilayered factors potentially related to the DFI and sperm image/video data, including standard semen analysis parameters, endocrine and metabolic biomarkers, environmental chemicals, physical measurements, and lifestyle factors, to support confounding adjustment and hypothesis generation in future phases (group 2).

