#### Sample Size

Considering biological sample processing, assay capacity, and the budget in this initial phase, the target group-specific enrollment was set at 25 for group 1 and 100 for group 2. Because co-enrollment was permitted, these targets refer to group-specific enrollment records; therefore, the total number of unique individuals across both groups may be smaller than the sum of the two group-specific counts. The two groups address different objectives. Group 1 is intended for quality control and descriptive characterization of the DFI measurement system in a relatively homogeneous low-risk population, rather than formal hypothesis testing. Group 2 is intended for feasibility-oriented initial association analyses between sperm image/video data and the DFI and exploratory analyses of candidate factors. Therefore, the sample size was determined pragmatically rather than via a formal power calculation for a specific effect size. We acknowledge that this initial phase may be underpowered to detect small associations or to support multivariable models with many predictors. Accordingly, effect estimates, CIs, and consistency of direction will be emphasized, and the findings will be used to inform variable prioritization and formal sample size planning for subsequent phases.

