#### Image Information Analysis

For the primary analysis, predefined microscopic sperm image-/video-derived summary variables will be assessed for association with the continuous DFI (primary outcome measure) as a preliminary proof-of-concept evaluation of whether image/video data contain information relevant to sperm DNA integrity. Associations with the continuous DFI will initially be assessed using correlation analyses and simple linear regression. When the DFI is categorized using prespecified literature-informed thresholds or a study-specific exploratory candidate threshold, simple logistic regression will be used as a secondary exploratory analysis. Any predictive modeling (including AI approaches) will be considered exploratory and will be specified in subsequent phases after database expansion. Exploratory image-DFI association analyses will be reported separately by group. If any additional pooled participant-level analysis across groups 1 and 2 is performed, the nonoverlapping dataset described earlier will be used.

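### The protocol contradicts itself on whether group 1 belongs to the primary image-DFI analysis, never says which group's result is primary, and justifies unadjusted testing only for secondary analyses

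*Protocol article*

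**What the plan says.** Two accounts of group 1 stand side by side in the protocol article.

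- **Group 1 inside the association analysis.** Abstract, Methods: "In groups 1 and 2, predefined image-/video-derived summary variables after standardized preprocessing will be analyzed against the continuous DFI". The second item under Study Objectives also attaches both groups to the initial image-DFI analyses. Image Information Analysis has these results reported for each group separately.
- **Group 1 outside it.** Under Sample Size, group 1 serves quality control and "descriptive characterization of the DFI measurement system in a relatively homogeneous low-risk population, rather than formal hypothesis testing", and the image-DFI association work is given to group 2. Descriptive Statistics and Data Preprocessing repeats the split: "group 1 is used for DFI quality control and group 2 for exploratory association analyses".

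The label also shifts. Definition of Outcome Measures and the opening of Image Information Analysis call the image-DFI association the primary analysis. Later in Image Information Analysis it is called exploratory.

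On testing, Descriptive Statistics and Data Preprocessing sets a two-sided nominal P<.05 for every test. It then explains, with reference to the secondary analyses, why "no formal multiplicity adjustment is planned". The primary analysis uses image variables in the plural, described as predefined; the article gives neither their number nor their names.

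On pooling: "If any additional pooled participant-level analysis across groups 1 and 2 is performed, the nonoverlapping dataset described earlier will be used". The only models named in that section are simple (one-predictor) linear and logistic regression.

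**The concern.** A proof-of-concept question needs one designated answer. Here two group-specific results, and possibly a pooled one, can each be presented as the primary image-DFI finding, and the text supports more than one choice. The two groups differ about fourfold in size, so the same observed correlation can look null in one and positive in the other.

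The multiplicity statement has a gap at the same place. It covers secondary analyses and is silent on the several image variables that make up the primary analysis, while P<.05 applies to all of them.

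The pooled analysis is a smaller matter. Study Design and Table 1 show that group 1 was selected on age, BMI, smoking and ejaculation frequency. If DFI and an image variable both differ between groups for those reasons, a one-predictor regression on the pooled men can show an association that exists within neither group.

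**Working it through.** **Counts (Results section).** 25 group 1 records + 103 group 2 records - 4 co-enrolled men = 124 unique participants, as stated. The default de-duplicated pool is 25 + (103 - 4) = 25 + 99. All sizes below are upper limits, because men without DFI or image data leave the primary analysis.

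**1. How much the choice of group matters.** The 95% CI is tanh(atanh(r) ± 1.96/√(n-3)), and atanh(0.30) = 0.3095. The value r=0.30 is illustrative; the protocol states no effect size.

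- Group 1: 0.3095 ± 1.96/√22 = 0.3095 ± 0.4179, giving -0.11 to 0.62.
- Group 2: 0.3095 ± 1.96/√100 = 0.3095 ± 0.1960, giving 0.11 to 0.47.

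Power at a true r of 0.30 is Φ(0.3095·√(n-3) - 1.96): 31% in group 1 and 87% in group 2. The correlation detectable with 80% power is tanh((1.96 + 0.84)/√(n-3)): 0.54 and 0.27.

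**2. Multiplicity within the primary analysis.** The number of variables k is an assumption. For independent variables, the chance of at least one P<.05 under no association is 1 - 0.95^k. The correlated cases were simulated at n=103 (4,000 runs, equal mutual correlation ρ).

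| k | independent | ρ=0.5 | ρ=0.8 |
|---|---|---|---|
| 5 | 22.6% | 19% | 13% |
| 10 | 40.1% | 29% | 17% |

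Correlation and simple linear regression do not double these counts, since Pearson correlation and one-predictor regression give the same P value.

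**3. Pooling with and without a group term.** Assume zero correlation within each group, and group means that differ by d within-group SDs in both DFI and the image variable. With p = 25/124 = 0.2016, p(1-p) = 0.161. The pooled correlation has size 0.161d²/(1 + 0.161d²), which at d=1 is 0.161/1.161 = 0.14. Type I error was simulated with 10,000 runs.

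| d (assumed) | size of pooled r | type I error, no group term | with group term |
|---|---|---|---|
| 0 | 0.00 | 4.7% | 4.9% |
| 0.3 | 0.01 | 5.3% | 5.1% |
| 0.5 | 0.04 | 7.6% | 5.1% |
| 0.8 | 0.09 | 17.8% | 4.6% |
| 1.0 | 0.14 | 33.8% | 5.2% |

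**The case against.** The strongest reply is that this is a feasibility phase with a pragmatic sample size. Estimates and intervals are to carry the interpretation, no clinical decision hangs on P<.05, and the image variables are said to be predefined. Their list may sit in the full protocol. The datasets are also defined: results come by group, and a pool is conditional and additional. All of this stands. It limits the harm, and it makes a mandatory familywise procedure a trade-off rather than the correction of an error. It does not reconcile the two accounts of group 1, and it does not supply the missing ranking.

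On the pool, the protocol states no wrong model. It is silent on a group term for an optional analysis, and simple regression is not expressly tied to the pool. The group indicator is therefore a safeguard to write in, and a reader should not take the silence as a planned mistake.

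Four stronger inferences are tempting, and the documents do not support them:

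- *De-duplication loses data.* The rule is "Under the primary handling rule, the group 1 record will be retained and the corresponding group 2 record excluded". An image-DFI pool needs only video and DFI, which the group 1 record can supply. Analyses that need blood, urine or physical data are group 2 analyses and keep all 103 records.
- *Agreement between groups is treated as replication.* Consistency of direction is emphasised, but nowhere as independent confirmation of one group by the other. Co-enrolled records are expressly not treated as independent in cross-group or pooled work.
- *The largest correlation will size the next phase.* The findings are to inform planning; no rule for selecting an estimate is given.
- *The pool is a third version of the primary analysis.* It is described only as additional.

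**Conclusion.** The point holds as an inconsistency in the wording that should be resolved before the association analyses, which are due by March 2028. Group 1's role in the primary image-DFI analysis is stated in two incompatible ways, no result is designated as primary, and the rationale for unadjusted testing does not reach the primary analysis.

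The firmest figure is the contrast in precision, which needs only the enrolment counts and an illustrative r=0.30: -0.11 to 0.62 against 0.11 to 0.47. The false-positive rates rest on assumed numbers of variables and assumed mutual correlations. The pooling figures rest on assumed group shifts. The documents give none of these. At a shift of 0.3 SD the pooling problem is negligible; it becomes serious only towards 1 SD, and Table 1 lets men of the group 1 type into group 2, which may keep the shift small.

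None of this shows that the study cannot meet its feasibility aim.

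**What to change.** 1. State consistently in the Abstract, Study Objectives, Descriptive Statistics and Data Preprocessing, and Image Information Analysis that the primary image-DFI analysis is in group 2 (n=103). State that group 1 image-DFI results (n=25) are descriptive estimates with CIs and no P values. Use one label, primary or exploratory, for the same analysis.
2. Extend the multiplicity statement to the primary analysis. Either say that its per-variable P values are unadjusted and exploratory and that every predefined image variable will be reported, or state an adjustment. The choice is the sponsor's.
3. Say that any pooled image-DFI model will include a group indicator.

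Cost: changes of wording only. Group 1 gives up P values that 25 men could not support, and the pooled model spends one degree of freedom. If the sponsor chooses a Bonferroni-type adjustment, the per-variable threshold falls to 0.05/5 = 0.01 for five variables or 0.05/10 = 0.005 for ten.
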